#### Independent Impact of Hypoglycemia

Generalized estimating equation (GEE) models will be used to investigate productivity losses and utility decrements associated with incident hypoglycemic events while controlling for individual patient characteristics. For utility, two separate models will be presented: one for the EQ-5D index and one for the visual analogue scale. For productivity losses, one main analysis will be presented for the total number, and separate models for each module will be presented as a complementary analysis. The potential model-confounding covariates are presented in Table S1 in Multimedia Appendix 1. Independent variables were identified based on existing literature and previous work from the Alliance for Canadian Health Outcomes Research in Diabetes [34]. Diabetes complications (micro- and macrovascular) to be included in the models are those preconized by HTA agencies for CUAs in T2DM [4,6,7]. On the basis of the current reference study for hypoglycemic utility values [5], the number of hypoglycemic episodes will be log-transformed to facilitate model fitting. The original scale will be tested using sensitivity analyses. Moreover, transformations of continuous independent variables will also be tested in the sensitivity analyses (Table S1 in Multimedia Appendix 1). The presence of multicollinearity will be tested, where important collinearity will be defined as a variance inflation factor of >10. Owing to the short duration of the study, all covariates, except hypoglycemia, will be considered time invariant for model simplicity. If vascular complications occur during the study period (incident cases), a history of macrovascular and microvascular complications will be treated as a time-varying covariate. The main models will not include interaction terms, as large-scale studies evaluating the impact of diabetes complications on utility have not demonstrated any interaction between vascular events and event history and among the different vascular events [35-37]. A sensitivity analysis will be performed to test for the interaction between hypoglycemic events and determinants, namely, a history of hypoglycemia and diabetes complications.

Distributions of outcomes will be examined considering the expected nature of productivity data (right-skewed and excess zeros) and utility data (left-skewed, censored, and ceiling effect). Although utility is commonly left-skewed, the distribution of utility scores may vary greatly between health conditions depending on the severity. Left skewness is more common when the studied condition is associated with mild symptoms, whereas severe health states may even lead to negative values representing conditions worse than death [38]. One major advantage of the GEE is the avoidance of distributional assumptions, where several distributions can be tested. Several large-scale longitudinal studies evaluating the impact of diabetes complications on utility, including the landmark United Kingdom Prospective Diabetes Study, used models fitted under a linear framework [35-37]. Common alternatives to the Gaussian distribution with identity link function include the Gaussian distribution with log link, negative binomial distribution with log link, gamma distribution with identity link, and gamma distribution with log link. The gamma distribution requires nonzero positive continuous data; thus, utility must be transposed into disutility (1−utility value). A beta binomial distribution can also be used with a transformation (linear transformation or rescaling) to fit the restrictive open interval (0,1), which excludes the end points 0 and 1 [39]. For the use of health care resources, nonlinear options mostly include negative binomial distribution (for resource use) and gamma and inverse-Gaussian distribution with log link function (for costs). Raw outcome data will be explored, where distributions will be depicted using histograms and normal probability plots. The selection of the model will be based on predictive performance and goodness of fit, with the lowest values for the root mean square error and the mean absolute error and the highest values for pseudo-*R*^2^. Moreover, the model performance will also be calculated using the quasi-likelihood under the independence model criterion (QIC), where the lowest values are the best. QIC and QIC*u* will be used for correlation structure selection and variable selection, respectively. As no distributional assumptions about the response variable are made, the regression parameters cannot be estimated using the maximum likelihood method. Thus, quasi-likelihood statistics will be used (pseudo-*R*^2^, QIC, and QIC*u*) instead of the well-known likelihood statistics (*R*^2^, Akaike information criterion, and Bayesian information criterion) [40]. Different variance-covariance structures are available to fit the relationship between responses. In health economics, common choices include exchangeable correlation structure (observations from the same cluster are equally correlated), autoregressive (correlation decreases with time), and unstructured (different and complex correlations). According to the Good Research Practices for Retrospective Database Analysis Task Force recommendations by the International Society for Pharmacoeconomics and Outcomes Research, if results are similar with different matrices, an exchangeable matrix will be used [41]. Regression diagnostics will be performed to explore the presence of influential observations and outliers (Cook distance and residual plots). Exclusion of extreme values will be tested in sensitivity analysis. All results will be expressed as coefficients, SEs, 95% CIs, and associated *P* values (2-sided tests at the .05 significance level). Full regression models and adjusted effects will be presented. All statistical analyses will be performed using R (R Foundation for Statistical Computing) [42].

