The outcomes will be measured using validated questionnaires. Although several instruments are available to estimate productivity losses, there is no gold standard [55]. In addition, HTA agencies make different recommendations regarding types of productivity losses (absenteeism, presenteeism, and unpaid work) to include in economic evaluations and methods for valuation or monetization (human capital approach and friction approach) [33]. Therefore, productivity losses will be presented as total and type-specific raw scores (number of hours per day) and will not be transposed into monetary value. This approach provides flexibility and allows future economic evaluations to be fit for specific purposes. The *i*PCQ scoring manual presents different valuation methods depending on various scenarios (eg, presence of long-term absences and frequency of measurements) and is fully adaptable to different HTA requirements [33]. It is recommended that the choice of a work productivity instrument for economic evaluations should be based on purpose, perspective, practicality, population, and psychometrics (5 *P*s) [55]. The *i*PCQ meets the 5 *P*s criteria as it is a validated generic instrument that allows monetization, captures all types of productivity losses, and minimizes the burden to patients (has short completion time and is easy to understand). Owing to its recent development, the use of the *i*PCQ is less extended than older questionnaires, which comes with the advantage that questions are optimized based on 3 previously validated instruments [33]. Moreover, this promising instrument has a recall period of 4 weeks, which matches measurements of hypoglycemia while limiting recall bias. Although there is no gold standard, the Work Productivity and Activity Impairment Questionnaire is the most widely used instrument to assess productivity losses [56]. Similar to the *i*PCQ, the Work Productivity and Activity Impairment Questionnaire covers absenteeism, presenteeism, and unpaid work, but over a shorter period. As the recall period is only 7 days, it may not capture all productivity losses due to hypoglycemia if events occur outside of the recall period. Regarding utility, the use of generic preference-based instruments is recommended, among which the EQ-5D is the most extensively used [57]. The EQ-5D asks patients how they feel on that day without any recall period. Therefore, for complications associated with transient effects only (eg, diarrhea), utility should be measured simultaneously (ie, on the same day). When acute events are followed by persistent fear and anxiety (eg, stroke), different measurement timings can be used. If the utility is measured shortly after the event, the punctual effect of the complication will be captured. If utility is not measured concurrently, then a general effect will be captured. For economic modeling of T2DM, utility values recommended by HTA agencies were all sourced from studies designed to capture the general impact of diabetic complications, including hypoglycemia [6,7]. In a reference study by Currie et al [5], the EQ-5D captured decrements in utility due to hypoglycemic events that occurred over the last 3 months. Furthermore, in several randomized controlled trials, the impact of SHEs on utility was measured for up to 1 year after the event [36,58,59]. A limitation of this approach is the underestimation of acute physical effects related to the event. Indeed, the current design may capture the psychological effects of hypoglycemia more accurately. Nevertheless, this study will estimate the overall impact of this treatment-related adverse effect on utility, providing relevant inputs for T2DM economic modeling.

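### QIC is named as a model-performance criterion without being limited to one variance family and outcome scale, although QIC values are comparable only within those limits

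*Protocol article*

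**What the plan says.** The Protocol article, Statistical Analysis, Independent Impact of Hypoglycemia, presents the choice of distribution as open: "One major advantage of the GEE is the avoidance of distributional assumptions, where several distributions can be tested". It then lists candidates: "Common alternatives to the Gaussian distribution with identity link function include the Gaussian distribution with log link, negative binomial distribution with log link", followed by gamma with identity and log links. For gamma, "utility must be transposed into disutility (1−utility value"). A further option is beta-type: "A beta binomial distribution can also be used with a transformation (linear transformation or rescaling") to bring the outcome into the open unit interval. Negative binomial, gamma and inverse-Gaussian models are also named for resource-use and cost-type outcomes.

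The selection rule follows: "The selection of the model will be based on predictive performance and goodness of fit". The measures named for this are RMSE and MAE, where lower is better, and pseudo-R², where higher is better. The next sentence opens with a connecting word and adds that "the model performance will also be calculated using the quasi-likelihood under the independence model criterion (QIC), where the lowest values are the best". The sentence after that gives QIC the choice of correlation structure and QICu the choice of variables.

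The same section calls for separate models for the EQ-5D index and the visual analogue scale. Under Measurement of Outcomes, Utility, the index has 1 as complete health and 0 as death, and the visual analogue scale runs from 0 to 100. Under Strengths and Limitations, productivity losses are to be given as "total and type-specific raw scores (number of hours per day").

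**The concern.** QIC is minus twice a quasi-likelihood plus a penalty. The quasi-likelihood is defined by the variance function, so Gaussian, gamma and beta-type models each have their own. Within one family and one outcome scale a lower QIC has a meaning. Between families, or between utility, 1−utility and a rescaled outcome, the difference partly reflects the unit in which the outcome is recorded.

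The QIC sentence continues the rule for choosing the model, and the role for correlation structure is stated separately afterwards. The more natural reading is therefore that QIC is a further criterion across all the listed models. If RMSE hardly separates them, QIC could settle the family and link for reasons unrelated to fit. The family and link determine the form of the decrement that goes into cost-utility models.

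**Working it through.** The plan states no figure on this point, so there is none to reproduce. The check is algebra, followed by simulation.

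**Inputs.** From the plan: the candidate families and the selection criteria (Independent Impact of Hypoglycemia); 400 patients after attrition (Sample Size) and three assessments (Assessments and Study Calendar), so n = 400 × 3 = 1,200. Assumed: all parameters of the simulated outcomes.

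**Formulas.** QIC = −2Q + 2·trace, with Q evaluated under independence and φ the dispersion.
- Gaussian: −2Q = Σ(y−μ)²/φ
- Gamma: −2Q = 2Σ(y/μ + ln μ)/φ

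**Change of unit from y to c·y.**
- Gaussian, φ = 1: the term is multiplied by c².
- Gaussian, φ estimated for each model: the term stays at about n − p, whatever the fit.
- Gamma: y/μ is unchanged and ln μ rises by ln c per record, so the term shifts by 2n·ln c (divided by φ if φ is estimated).

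The QIC difference between the two families therefore moves with c, although the data and the fit do not.

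**One gamma-generated data set, exchangeable GEE, only the unit changed:**

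| Unit | φ | Gaussian-identity QIC | Gamma-log QIC | Lower |
|---|---|---|---|---|
| Hours per 4 weeks | estimated | 1,208.9 | 7,426.2 | Gaussian |
| Hours per day (÷28) | estimated | 1,208.9 | −586.7 | Gamma |
| Hours per 4 weeks | 1 | 101,813.5 | 7,411.7 | Gamma |
| 8-hour days (÷8) | 1 | 1,590.8 | 2,421.1 | Gaussian |
| Hours per day (÷28) | 1 | 129.9 | −585.6 | Gamma |

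The algebra accounts for these values. With φ = 1 the gamma shift from hours per 4 weeks to hours per day is 7,411.7 + 585.6 = 7,997.3 = 2 × 1,200 × ln 28. The Gaussian value in 8-hour days is 101,813.5/64 = 1,590.8. RMSE in hours per 4 weeks was 9.166 (Gaussian-identity) against 9.143 (gamma-log), a gap of about 0.3%, with the same order in every unit.

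**60 replicates per setting, share preferring Gaussian-identity to gamma-log:**
- Gamma-generated, φ estimated: 100% in hours per 4 weeks, 0% in hours per day.
- Gaussian-generated, φ = 1: 100% in hours per 4 weeks, 0% in minutes.
- RMSE: 38% of gamma-generated and 67% of Gaussian-generated replicates, the same in every unit tested.

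**Disutility on 0–1 against 0–100, one data set.** With φ estimated, Gaussian QIC is 1,206 on both scales. Gamma QIC goes from −2,339 (gamma lower) to 17,287 (Gaussian lower). With φ = 1 gamma is lower on both scales (−1,317 against 32; 9,735 against 319,427), so this data set reverses under one convention only. Two further simulations with other assumed parameters reversed under both. Gamma was chosen in 95% then 0% (20 data sets) and in 67% then 0% (30 data sets) with φ estimated, and in 0% then 100% in both with φ = 1.

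**Within one family.** Adding a covariate lowers gamma QIC by 39.8 in all three units tested (7,451.5 to 7,411.7; −545.8 to −585.6; 17,277.9 to 17,238.2). The criterion is sound there.

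**Effect on the estimate.** In a simulation of gamma disutility (40 data sets), the mean decrement from 0 to 1 event was 0.0175 (Gaussian-identity) against 0.0162 (gamma-log). The gap of 0.0013 compares with a sampling SD of about 0.004. In another simulation the two decrements differed by about 1–4%.

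**The case against.** The strongest reply is textual. The article never says in so many words that distributions are ranked by QIC. RMSE, MAE and pseudo-R² come first, and the sentence after the QIC statement gives QIC a proper role, the correlation structure. On that reading nothing is wrong beyond loose wording. This stands as a limit: a reader might infer an explicit rule to rank families by QIC, and the text does not go that far. It does not remove the point, because the QIC sentence is attached to model selection and carries no restriction to one family or scale.

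Second, the units are fixed. The index has its anchors, and productivity is in hours per day. A reader might infer that this study's data would yield two different models depending on the unit chosen. Nothing in the article proposes such a change, so the rescaling is an illustration only. In hours per day, QIC in fact favoured the generating family in all replicates of both types. That is an accident of the unit and the assumed parameters: fixing a unit fixes the arbitrary term but does not remove it. The index, the visual analogue scale, 1−utility and the rescaled outcome remain on different scales under the one rule.

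Third, a reader might infer that MAE would select a wrong model, since zero is the constant that minimises MAE when most windows show no loss. This is not supported. No candidate predicts a constant zero; all are models for the mean. In a simulation with 66% zeros (parameters assumed), the model with the lowest MAE also had the lowest RMSE, and its mean prediction was 2.864 against 2.880 observed.

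Fourth, the demonstrated effect on the decrement is small. That stands.

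**Conclusion.** The point holds in a limited form. The article offers lowest QIC as a measure of model performance next to a list of different variance families and transformed outcomes, and does not confine it to models for which it is comparable. Where RMSE is nearly tied, as in the simulations, QIC could choose the family by scale rather than fit, and could point to different families for the index and the visual analogue scale for that reason alone.

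The scale dependence follows from the formulas and needs no simulation. The unit at which the ranking turns, and the percentages, depend on the assumed parameters and on whether dispersion is fixed or estimated. The gamma simulations carry neither the ceiling effect nor the excess zeros that the plan expects. A reader might infer that the published decrement would be materially wrong. The evidence does not show this: the largest gap found was about one third of a sampling SD (0.0013/0.004). This is a minor to moderate correction.

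**What to change.** Reword the QIC sentence so that QIC and QICu serve only to choose the working correlation and the covariates within one chosen family, link and outcome scale. The following sentence already gives them that role. Choose family and link by RMSE and by observed against predicted means across event-count groups, with all predictions transformed back to the original outcome scale and computed on the same records. MAE may still be reported but should not override RMSE, because the economic input is a mean.

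The cost is a change of wording and one fewer criterion for choosing the family. RMSE may often be nearly tied, and the comparison of observed with predicted means is there to inform that case. No data collection or sample size is affected.

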### Measurement of Outcomes

#### Utility

The EQ-5D-5L questionnaire will be used to measure the utility values [25,26]. This validated instrument is widely used and covers five dimensions (mobility, self-care, usual activities, pain or discomfort, and anxiety or depression) that are further divided into five levels (no problems, slight problems, moderate problems, severe problems, and extreme problems). The EQ-5D (EQ-5D) health states may be converted into a single summary index through a crosswalk value set. An EQ-5D summary index of 1 represents complete health, 0 represents death, and negative values represent states worse than death. The questionnaire also includes a visual analog scale that records the respondent’s self-rated health using a vertical scale ranging from 0 to 100 with end points labeled as “the best health you can imagine” and “the worst health you can imagine.” EQ-5D scores represent patients’ health status on the day of questionnaire completion.

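### QICu may drop pre-identified confounders from a model meant to isolate the effect of hypoglycemia, the gamma option contradicts itself at full health, and the reporting scale is not fixed

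*Protocol article*

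**What the plan says.** All of this stands in the Protocol article, mainly under Independent Impact of Hypoglycemia.

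- **Covariates.** Potential confounders are listed in Table S1 (not shown) and were identified from the literature and earlier Canadian work. The diabetes complications are described as ones to be included; the rest are only potential.
- **Variable selection.** QIC and QICu "will be used for correlation structure selection and variable selection, respectively".
- **Distribution and link.** "The selection of the model will be based on predictive performance and goodness of fit", judged by RMSE, MAE and pseudo-R², with QIC as a further measure. The criteria are not ranked. The candidates are Gaussian with identity or log link, negative binomial with log link, "gamma distribution with identity link, and gamma distribution with log link", and a beta binomial option.
- **Gamma.** "The gamma distribution requires nonzero positive continuous data; thus, utility must be transposed into disutility", defined as 1 minus utility. For the beta option a transformation is given "to fit the restrictive open interval (0,1), which excludes the end points 0 and 1"; none is given for gamma.
- **Full health.** Under Utility: "An EQ-5D summary index of 1 represents complete health". The analysis section expects "utility data (left-skewed, censored, and ceiling effect".
- **Reporting.** Coefficients, SEs, 95% CIs and P values, plus full models and adjusted effects, on no stated scale.

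**The concern.** QICu rewards prediction of the outcome. A confounder biases the hypoglycemia coefficient through the product of its links with exposure and with outcome. One with a clear link to event frequency and a modest link to utility can therefore fail the criterion and still matter. Under Strengths and Limitations, the protocol relies on every known confounder having been measured, and its E values are defined as above and beyond the measured covariates. Measuring a confounder and then removing it weakens both arguments. The SE is also calculated as if the retained set had been known beforehand.

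Research Purpose and Study Design promises estimates with CIs and SEs for use in cost-utility models. Study Rationale and Relevance says incremental cost-effectiveness ratios are very sensitive to these decrements. The size, the SE and the scale of the coefficient are therefore what the study is meant to deliver.

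**Working it through.** **Size of the study.** The plan's own figures reproduce: 68 / 0.17 = 400 patients, and 400 / (1 − 0.20) = 500 enrolled. The simulations use 400.

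**1. Selection by QICu, repeated-measures version.** Assumed, because Table S1 is not shown: 15 confounders, each raising the log event rate by 0.15 or 0.20 per SD and lowering utility by 0.005 or 0.01 per SD. The true coefficient is −0.014 per unit of log(1 + events). There are 400 patients with 3 visits each, fitted by Gaussian identity GEE with independence working correlation and cluster-robust SE. QICu was taken as RSS/φ + 2p (φ from the full model), with backward elimination and 2000 replicates per setting.

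| Rate effect / utility effect | Covariates kept | Bias | Mean SE / empirical SD | Coverage |
|---|---|---|---|---|
| 0.15 / −0.005 | all 15 | 1% | 0.0099/0.0100 = 0.99 | 94.4% |
| | QICu (7.0) | 14% | 0.0097/0.0100 = 0.97 | 93.5% |
| 0.15 / −0.01 | all 15 | 0% | 0.0099/0.0104 = 0.95 | 93.3% |
| | QICu (10.3) | 14% | 0.0097/0.0107 = 0.91 | 91.1% |
| 0.20 / −0.005 | all 15 | 2% | 0.0099/0.0105 = 0.94 | 92.6% |
| | QICu (6.9) | 18% | 0.0094/0.0106 = 0.89 | 89.9% |

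Bias is away from zero because every assumed confounder raises events and lowers utility. Coverage lost to selection is 0.9, 2.2 and 2.7 points.

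**2. How far this depends on the confounders.** A simpler proxy used one record per patient, 17% exposed, a true effect of −0.060 and backward AIC in place of QICu. With 20 weak confounders in one direction (exposure OR 1.22 and utility −0.012 per SD) and 600 replicates, full adjustment gave −0.060 with 95% coverage. Selection kept about 9 of 20 and gave −0.071 with 90% coverage: (0.071 − 0.060)/0.060 = 18%, and 5 points lost. Varying the confounders (residual SD 0.2, 400 replicates, so coverage is known to about ±1 point) gave, after selection:

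| Confounders | Estimate | Coverage |
|---|---|---|
| 20 weak, one direction | −0.070 | 91% |
| 15 one way, 5 the other | −0.065 | 93% |
| 10 each way | −0.060 | 93% |
| 8 stronger (−0.04 per SD), 7.9 kept | −0.059, as with full adjustment | 94.5% |
| 5 strong, 15 linked to exposure only | −0.062, as with full adjustment | 97% |

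**3. Gamma at full health.** Utility = 1 gives 1 − 1 = 0, which is not a nonzero positive value. R, the protocol's software, stops with an error when a Gamma GLM is given a zero. The share of patients at full health is not given, so simulated shares of 9%, 19% and 35% were used. If those records were dropped to make the model run, the average effect, compared with a linear fit to all records, would go from 0.0155 to 0.0130, from 0.0118 to 0.0068, and from 0.0108 to 0.0074. Adding a constant of 0.001 to 0.05 instead leaves the average effect at the 35% share at 0.0103 to 0.0104, but moves the log coefficient from 0.077 to 0.057.

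**4. Scale.** With a log link on disutility d, a coefficient b changes utility by d × (exp(b) − 1). For b = 0.10 the factor is 0.105, so the decrement is 0.005, 0.011, 0.021 or 0.042 at d = 0.05, 0.10, 0.20 or 0.40. The coefficient does not correspond to one decrement.

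**The case against.** The strongest reply is that the size of the harm rests entirely on inputs nobody outside the study can see. That stands. The number, strength and direction of the covariates are assumptions. Strong confounders are almost always retained, mixed directions largely cancel, and dropping a variable unrelated to the outcome costs nothing because it is not a confounder. The protocol does not say that QICu will drive backward elimination; it may only compare a few candidate sets. The diabetes complications appear safe from removal.

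A reader might infer that the main coefficient will be about 18% too large and clearly over-precise. The documents do not support that: 18% is the top of a range that starts near zero. SE understatement was 3–11% with selection against 1–6% without, so part of it is not due to selection.

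A reader might also infer that the result will not be on the utility scale. Gaussian identity is among the candidates and has cited linear precedents. Gamma with identity link on disutility is also additive, with the sign reversed. The adjusted effects could restore the scale, though the text does not say so.

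Finally, no section plans to drop full-health records. The figures for that case show what one workaround would do, and the gamma quasi-score is itself finite at zero. The contradiction with the protocol's own requirement remains.

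Choosing a distribution from the data is a defensible plan for skewed, ceiling-limited outcomes. That does not extend to choosing confounders by fit.

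**Conclusion.** The point holds as a conditional risk and a definite wording error. The text makes QICu the rule for variable selection, which conflicts with estimating an independent effect adjusted for pre-identified confounders, and nothing in the planned SEs or CIs allows for the selection. Under assumed confounders the cost is about 0 to 18% bias and 0 to about 5 points of coverage. It approaches the upper end only when many weak confounders act in the same direction, and may be negligible otherwise.

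The gamma contradiction needs no simulation: it follows from the protocol's own definitions, taking full health to score exactly 1 as the Utility section states. Its effect on the results depends on whether gamma is chosen and how zeros are then handled. The scale problem arises only if a log-link or rescaled model is selected and adjusted effects are not given in utility units. The changes are worth making before analysis because they are nearly free and protect the quantities the study promises.

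**What to change.** 1. Keep the full pre-listed confounder set in the main utility and productivity models regardless of QICu. Present QICu-reduced models as sensitivity analyses only.
2. Name the primary utility model in advance. Gaussian with identity link and robust SEs is the natural choice, given the linear precedents the protocol cites. Keep the other distributions as sensitivity analyses.
3. Report every model as average marginal effects with SEs on the original utility or hours scale, fitted to identical observations so that fit statistics are comparable.
4. Remove gamma on 1 minus utility, or state a valid way to handle utility = 1 that does not drop those records.

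The cost is wording. Keeping weak covariates may enlarge the SEs slightly. In the simulations full adjustment did not increase the spread of the estimate (0.0269 against 0.0277 after selection in the 20-confounder proxy; 0.0100 to 0.0105 against 0.0100 to 0.0107 in the repeated-measures version), but that rests on 15 to 20 assumed covariates and 400 patients.

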#### Assessments and Study Calendar

Patients will complete a self-assessment questionnaire (SAQ) at 4, 8, and 12 weeks to report the number of NSHEs and SHEs experienced in the last 28 days. Patients will also be provided with a diary to prospectively record hypoglycemic events. Both the SAQ and the diary will be used to estimate the number of hypoglycemic events. The EQ-5D and *i*PCQ will also be completed at 4, 8, and 12 weeks. The study calendar is shown in Figure 1. The questionnaires will be completed electronically via a web-based platform. To ensure that patients complete their questionnaires in a timely manner, reminders will be sent to them via email. Paper-based questionnaires can be provided to participants who do not have access to or are less familiar with using the internet (phone call reminders).

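### As described, the utility model has no term for events in earlier study windows, so a lasting effect of severe hypoglycemia is biased toward zero and the matrix-similarity rule cannot reveal it

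*Protocol article*

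**What the plan says.** **Target.** Under Definition of Hypoglycemia, the study sets out to estimate the total effect on utility, meaning the passing effect of an event plus the fear that follows it. Strengths and Limitations defends measuring utility away from the event. It cites a reference study with a three-month event window and trials in which "the impact of SHEs on utility was measured for up to 1 year after the event".

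**Exposure and outcome.** Under Assessments and Study Calendar, patients complete a questionnaire "at 4, 8, and 12 weeks to report the number of NSHEs and SHEs experienced in the last 28 days". The EQ-5D "will also be completed at 4, 8, and 12 weeks", and under Utility, "EQ-5D scores represent patients’ health status on the day of questionnaire completion".

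**Model.** Independent Impact of Hypoglycemia says that "the number of hypoglycemic episodes will be log-transformed to facilitate model fitting" and that "all covariates, except hypoglycemia, will be considered time invariant for model simplicity" (vascular history may also vary if incident cases occur). Strengths and Limitations calls the exposure time-varying. No lagged or cumulative in-study term is described.

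**Working correlation.** The same section names exchangeable, autoregressive and unstructured structures as common choices, uses QIC to select among structures, and adds that "if results are similar with different matrices, an exchangeable matrix will be used".

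**The concern.** Take a patient with an SHE in weeks 1–4 and none later. On the natural reading, this patient counts as event-free at weeks 8 and 12. By the plan's own argument, utility may still be lowered at those visits.

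With a time-varying exposure, a GEE with a non-diagonal working correlation is consistent only if each visit's mean depends on that visit's covariates alone. Carry-over breaks this condition. The non-diagonal weights draw on within-patient contrasts, and those contrasts set affected visits against other affected visits that are coded as unexposed.

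The SHE utility value is the quantity the study is sized on, and Study Rationale and Relevance says that cost-effectiveness ratios are very sensitive to it. The limitation the plan admits is underestimation of acute physical effects. Here the lasting component, which the design claims to capture better, is the one lost.

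**Working it through.** **1. Inputs from the protocol.** Three 28-day windows; three-month SHE incidence of 17%; 68 patients with an SHE. The sample size reproduces: 68 / 0.17 = 400 and 400 / (1 − 0.20) = 500. With constant risk, the per-window probability is 1 − 0.83^(1/3) = 0.060.

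**2. Assumed inputs.** The documents give no within-patient correlation ρ and no degree of persistence. I take ρ from 0.3 to 0.9, and persistence from none to full.

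**3. Formula.** The large-sample GEE slope is the second element of {E[X′WX]}⁻¹ E[X′WY], where W is the inverse working correlation. The expectation runs over all 8 patterns of SHE yes/no in three windows. X holds an intercept and current-window SHE. Y falls from the first SHE window onward, and a repeat SHE adds nothing.

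**4. Result: estimated / true decrement.**

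| ρ | Exchangeable, fully lasting | AR(1), fully lasting | Exchangeable, 50% carried to each next window | AR(1), 50% carried |
|---|---|---|---|---|
| 0.3 | 0.733 | 0.764 | 0.887 | 0.885 |
| 0.5 | 0.640 | 0.660 | 0.848 | 0.832 |
| 0.7 | 0.570 | 0.575 | 0.818 | 0.789 |
| 0.9 | 0.514 | 0.510 | 0.794 | 0.755 |

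Independence gives 0.941 (fully lasting) and 0.975 (50% carried). With a purely transient effect, every structure gives 1.000. Adjusting for visit changes none of these values. If repeat effects add, the top of the 50% range is about 0.90.

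**5. Hand check.** For three visits, exchangeable W is proportional to I − θJ, with θ = ρ/(1 + 2ρ). If lasting effects add and windows are independent, the ratio is (1 − 2θ)/(1 − θ) = 1/(1 + ρ). At ρ = 0.7 this is 0.588, slightly above the 0.570 found when a repeat SHE adds nothing. The pure within-patient limit is one half: an SHE in window 1 contributes 0, in window 2 half the effect, and in window 3 all of it, and (0 + ½ + 1)/3 = ½.

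**6. Simulated fits.** Exchangeable GEE fits with overdispersed SHE counts (4,000 patients, 25 replicates) gave 0.63, 0.57 and 0.57 at ρ = 0.5, 0.7 and 0.8. A separate simulation used 400 patients, a true decrement of 0.060, SD 0.20 and ρ = 0.7. Under full persistence, exchangeable, AR(1) and unstructured all gave 0.034, and 0.034/0.060 = 0.57. Coverage of the 95% CI was 61–64%.

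**7. Why coverage falls.** The bias is 0.060 − 0.034 = 0.026, and 0.026 / 0.016 ≈ 1.6 SEs. A shift of that size alone predicts coverage of roughly 60%. The interval is centred too close to zero; the SE need not be wrong.

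**8. The similarity rule.** At ρ = 0.7, exchangeable and AR(1) differ by 0.575 − 0.570 = 0.005 of the true effect while about 43% of a lasting effect is lost.

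**The case against.** - **The coding is inferred.** No sentence says that the week-8 and week-12 regressors exclude earlier events. The covariate list is in Table S1 of the appendix, which is not shown, and lag coding may be left to an analysis plan. This stands as a qualification. Still, the 28-day recall, the same-visit EQ-5D and the time-varying exposure all point one way. The baseline history of hypoglycemia is recorded at recruitment and cannot carry in-study events.
- **Full persistence is not the plan's premise.** The target mixes transient effects with fear, and a measurement up to one year after an event is not a claim of an undiminished effect. This stands. A reader might infer that the SHE decrement will be estimated at about half its size. That needs a fully lasting effect and ρ of about 0.6 or more, and the documents fix neither.
- **Independence is not excluded.** The three structures are offered as common choices, and QIC selects. This is true, but independence is not named, and the default applies once results agree.
- **Falsely narrow intervals.** A reader might infer these from the low coverage. The shifted centre explains it.
- **An independence fit may itself mislead.** In an illustrative case with no persistence but between-patient confounding, exchangeable gave 1.07 of the truth and independence 1.36. A gap between the two fits is therefore not specific to carry-over.
- **Scale.** The main model uses log counts, so sizes computed for SHE occurrence do not transfer directly. This stands.

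**Conclusion.** The concern holds in mechanism and direction, and its size is conditional. If the exposure is the current 28-day count, any persistence of the effect biases the SHE coefficient toward zero under the named working correlations. For ρ of 0.3 to 0.9, the model returns about 51–76% of a fully lasting decrement (a few points more if repeat effects add), about 76–90% with half carried over, and 100% if the effect is transient.

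This rests on constant SHE risk per window, SHE coded as occurrence, and assumed values of ρ and persistence. Uneven risk between patients barely changes it (0.56 instead of 0.57 at ρ = 0.7, exchangeable). The planned comparison of matrices cannot detect the problem, because the structures it names agree on nearly the same attenuated value.

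**What to change.** 1. State the exposure window that each visit's event count covers in the model.
2. Add cumulative prior-window SHE and NSHE counts since enrolment beside the current-window counts, on the same scale. Report the current and carried-over decrements separately.
3. As a sensitivity analysis, code any SHE since enrolment, in case repeat effects do not add. This recovers 1.00 of a lasting, non-additive effect but would understate one that fades.
4. Report an independence working correlation with robust SEs as a diagnostic only. Say in advance that a gap from the exchangeable result may reflect carry-over or between-patient confounding.

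With the prior-window term, the current-window SHE coefficient comes to 0.92–1.01 of the truth over the patterns checked. It is exact when a constant carried-over effect adds across events, and 0.92–0.94 when a fully lasting effect does not add. It is therefore not unbiased in every case.

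**Cost.** Analysis wording and derived variables from data already collected. No baseline EQ-5D is needed, and none is scheduled. The SE of the current-window SHE term rises modestly, from about 0.016 to 0.018 in the 400-patient simulation.
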